## Abstract

**Background:**

Prolonged sitting is ubiquitous in modern society and linked to several diseases. Height-adjustable desks are being used to decrease worksite based sitting time (ST). Single-desk sit-to-stand workplaces exhibit small ST reduction potential and short-term loss in performance. The aim of this paper is to report the study design and methodology of an ACTIVE OFFICE trial.

**Discussion:**

This study evaluates the effects of a novel two-desk sit-to-stand workplace on sitting time, physical parameters and work performance of healthy office based workers. If the intervention proves effective, it has a great potential to be implemented in regular workplaces to reduce diseases related to prolonged sitting.

**Trial registration:**

ClinicalTrials.gov Identifier: NCT02825303, July 2016 (retrospectively registered).

## Background

Prolonged sitting is ubiquitous in modern society and the amount of physically inactive people is rising in many countries [1, 2]. Ongoing computerization is a main cause for changes in physical activity and sitting time patterns [3, 4]. Screen time, which is commonly associated with sitting, has been dramatically increased by a rising prevalence of computers in school and occupational environments [4]. Duration of sitting time has also been shown to increase with age [5].

In 2013, 11 % of all European citizens (aged 14 years and older) spent more than 8.5 h per day in a sitting posture [6]. In the working age population, white-collar workers are most frequently affected by this amount of sitting time (21 %) and exhibit a more than four times higher risk of being exposed to prolonged sitting in comparison to manual occupations [6]. Especially office workers and call center employees are affected by prolonged sitting periods. The total amount of sitting in these occupations can exceed more than 80 % of the working day [7, 8].

Prolonged sitting is a risk factor for cardiovascular and musculoskeletal diseases, diabetes, several types of cancer and all-cause mortality [9–14]. In combination with static and awkward postures, the prevalence of musculoskeletal diseases (e.g. back pain, chest pain) can increase further [14]. As additional physical activity cannot fully compensate the effects of prolonged sitting [15, 16], standing between prolonged sitting periods and reduction of sedentary pursuits should be a goal for adults, irrespective of their exercise habits [17].

Given that most of the world’s population spend averagely one third of their adult life at work [18], it seems clear that worksite based interventions for reducing sitting time are key elements of daily sitting time reduction. Generally, worksite based recommendations in offices contain “*Sit less”, “Stand up”, “Move more” and “Change postures regularly*” [16, 19, 20]. In order to fulfill postural recommendations different types of worksite based interventions have been started. Besides numerous activity promotion programs, which typically replace sitting time with low-intensity physical activity [21], the implementation of sit-to-stand or active workstations is commonly used to diminish occupational sitting time [22].

Large differences in sitting time reduction have been found for different types of sit-to-stand workstations [22]. While non-significant changes in sitting time for sit-to-stand desk users in open plan offices occurred [23], meta-analysis showed an average reduction in sitting time of 77 min per 8-h workday for activity-permissive workstations [22]. Multi-component interventions (e.g. management consultation) can further enhance this effect [24].

Although the implementation of sit-to-stand or active workstations can help to reduce sitting time, improve physical activity at work and promote health benefits [25–27], it might also lead to changes in cognitive functions such as productivity [22]. Even though non-significant changes in attention have been found [28], fine motor functions (e.g. mouse moving) as well as mathematical problem solving can be negatively influenced by additional body movements [29]. As studies reporting deterioration of work-related outcomes were all of short duration, studies using long-term follow-up were recommended [22].

The occupational hazards associated with prolonged sitting are receiving renewed attention, and new technologies, devices, and workplace controls to help reduce sitting time are being developed and introduced regularly. It would benefit researchers, practitioners, and employers if these devices and controls were evaluated and studied using consistent and reproducible methods. Reliable and comparable information produced from similarly designed studies would help to separate fact from fiction in the efforts to reduce chronic sitting in the workplace.

### Objectives

The primary objective of this paper is to describe and discuss the methods of a study designed to evaluate the long-term effect of a novel two desk sit-to-stand workplace on sitting time as well as physiological and cognitive parameters for healthy people of working age in comparison to their traditional workplace (control). A secondary objective is to propose methods for future studies of sit-to-stand equipment and intervention programs.

### Hypothesis

The primary hypothesis of the described study is that the ACTIVE OFFICE two-desk sit-to-stand workplace are more effective in reducing occupational sitting time than conventional one desk solutions. Secondary hypotheses are that people using the ACTIVE OFFICE setup will experience positive long term effects on physiological and cognitive skills. The experimental groups received a two desk sit-to-stand workstation in their regular office environments.

## Methods/Design

ACTIVE OFFICE is a three-arm randomized control trial with two intervention and one control group (Fig. 1). After the baseline assessment was completed, the participants were randomly allocated to either the intervention or the control arm in a 2:1 ratio. The experimental group subjects received a novel two desk sit-to-stand workstation in their regular office environments, while the control group subjects did not encounter any change in their regular office environments. A 6-week wash out phase was implemented to encourage similar starting conditions for each participant (i.e. using a traditional workplace prior to pre-intervention measurements).

**Fig. 1 Fig1:**
[figure not shown]
ACTIVE OFFICE study design flow chart

### Participants

A convenience sample of participants was recruited from companies in Linz (Austria) and the surrounding area. A general letter requesting collaboration and providing study descriptions was sent to employers. To reduce recruiting bias, partner-company allocation was randomly done via a regional health insurance provider between August and September 2013. Study details were provided to companies that accepted collaboration in the form of information seminars located at the respective company sites. Separate interviews with people interested in participating in the study took place after the seminars to ascertain the potential subjects’ suitability for study purposes. After exclusion criteria were applied, participants were allocated randomly either to intervention or control groups.

### Subject inclusion criteria

Included subjects were: a) healthy caucasian (no acute or chronic diseases); b) normal weight or slightly overweight (BMI: 18.5–27.5 kg/m^2^); c) aged: 18–60 years; d)regularly working in sedentary office environments; e) regular computer users; f) fluent German speakers; and g) consented to participate.

### Subject exclusion criteria

Excluded subjects had or were: a) heavily overweight & Obesity (BMI >27.5 kg/m^2^); b) short office stay duration (<8 h / day or <20 h / week) c) experience in sit-to-stand workstations; d) acute or chronic diseases; e) inability to stand; f) visual impairments that had not been corrected; g) color blindness h) women who are pregnant or plan to become pregnant within 12 months; i) people planning to change their physical activity level; j) regular smokers (> 1 cigarette /day); or k) not consented to participate.

### Randomization and blinding

After the baseline assessment was completed, the participants were randomly allocated to either the intervention or the control (no intervention) arm in a 2:1 ratio (Fig. 1) by means of a covariate adaptive randomization [30]. Based on previous findings [31], ‘company’ has been determined as a stratum and thus participants were balanced across companies (i.e., 3 participants for each company). On a second level, intervention participants were assigned to either the first (intervention first) or the second (control first) intervention group. Due to the nature of the intervention, participants were not blind to their allocation.

### Sample size

A pilot study with 5 participants, performed in order to estimate the potential of the two-desk setup, found a 22 % reduction of sitting time [32]. Converted to a regular 8-h work day this results in 105 min of sitting time reduction. As this effect was noticeably higher than the effect shown by existing meta-analysis [22] we decided to detect a value between those limits. Therefore, 12 subjects would be needed to detect 90 min differences in sitting time, assuming an alpha risk of 0.05 and beta risk of 0.20 in a two-sided test, and with 20 % loss to follow-up.

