### Outcomes

Primary outcomes were changes in sitting time after 23 weeks in the experimental group compared with its own control period and the control group.

Secondary outcomes within the experimental group were changes in: reaction time, working speed, level of attention, workload perception, physical activity and postural changing pattern for the intervention phase as compared to the control phase.

Tertiary outcomes were changes in salivary cortisol level and heartrate variability (HRV) within the experimental group.

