### Statistical analysis

Statistical analyses will be conducted using SPSS version 21 for windows (SPSS, Chicago, IL). Standard statistical methods will be used for calculations for means and standard deviations. Pre- and post- intervention differences will be calculated for sitting time and physical parameters. Paired t-tests will be used to show differences between pre- and post- conditions when the normality condition is satisfied. If not, Mann-Whitney-U tests will be used for pre-post comparison. For cognitive parameters, ANOVA with repeated measures will be used to test whether the different conditions have any effects on the outcome parameters assessed. To reduce learning effects the first block of the test-battery will be ruled out for analysis. When appropriate, post-hoc analyses will be conducted. The effects of time, group and interaction between both variables will be evaluated. To test for normality and homogeneity of variance, Shapiro-Wilk-test and Levene-test will be used, respectively. In general, two-sided tests with an alpha risk of 0.05 and a beta risk of 0.2 are to be accepted.

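### The 80% power stated for 12 subjects fits only the within-person half of the primary outcome, and on that reading the comparison with 6 controls falls short of 80%; the 105-minute upper limit behind the 90-minute target depends on an unstated base for the 22%

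*Protocol article*

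**What the plan says.** The Sample size section of the protocol article states that "12 subjects would be needed to detect 90 min differences in sitting time, assuming an alpha risk of 0.05 and beta risk of 0.20". The calculation is two-sided and allows for 20% loss. The section names neither an SD nor a test, and does not say which comparison the figure serves.

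The 90 min was chosen to lie between a meta-analysis effect (77 min per 8-hour day, given in Background) and the effect in a five-person pilot, described as a 22% cut in sitting time. Of the pilot effect the section says: "Converted to a regular 8-h work day this results in 105 min of sitting time reduction".

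The Outcomes section makes the change in sitting time in the experimental group primary, "compared with its own control period and the control group". That is two contrasts. The Abstract gives 18 participants and Randomization and blinding gives a 2:1 ratio, hence 12 experimental and 6 control.

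The Statistical analysis section names paired t-tests for pre-post differences in sitting time, mentions effects of time, group and their interaction, and closes: "In general, two-sided tests with an alpha risk of 0.05 and a beta risk of 0.2 are to be accepted".

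**The concern.** One sample size and one power figure stand in front of a primary outcome with two comparisons of very different precision. One uses 12 people as their own controls; the other sets them against 6 others. The stated 12 equals the experimental arm, so the 80% appears to belong to the first comparison only. The closing sentence of the Statistical analysis section then attaches a beta risk of 0.2 to tests in general, and the Discussion lists the power analysis as a strength. A reader could take a non-significant comparison with controls as an 80%-powered negative result.

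The second doubt is the target itself. Multiplying 22% by a full 480 min treats the entire working day as sitting time. Background gives a different picture of office work: "The total amount of sitting in these occupations can exceed more than 80 % of the working day". If the 22% is a share of sitting time, the pilot effect in minutes is smaller, and 90 min may lie above the range from which it was meant to be chosen.

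**Working it through.** **Inputs.** From Sample size: two-sided alpha 0.05, power 0.80, difference 90 min, 20% loss, 22% pilot effect. From the Abstract and Randomization and blinding: 18 at 2:1, so 12 and 6. From Background: 77 min, and a sitting share that can exceed 80%. No SD is given, so the 12 cannot be computed forward. It can only be solved backwards for the SD that makes it true.

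**1. SD implied by the paired reading.** Completers: 12 × 0.8 = 9.6. Nine completers inflate to 9 / 0.8 = 11.25, rounded up to 12; ten inflate by 10 × 1.2 = 12. For a paired t-test, power = P(T > t0.975), with T noncentral t on n − 1 df and noncentrality (90 / SD) × √n.

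- n = 9: 80% power needs 90 / SD = 1.067, so SD = 84.4 min.
- n = 10: 80% power needs 90 / SD = 0.996, so SD = 90.4 min.

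**2. Control-group contrast with the same SD.** Two-sample t-test, noncentrality 90 / (SD × √(1/n1 + 1/n2)), df = n1 + n2 − 2. For example, at 10 v 5 and SD 90.4: 90 / (90.4 × √0.3) = 1.818 on 13 df, giving 39%.

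| SD (min) | 12 v 6 | 10 v 5 |
|---|---|---|
| 84.4 | 52% | 44% |
| 90.4 | 47% | 39% |

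**3. Sensitivity to the equal-SD assumption.** If the quantity compared between groups has SD s, and its values in the two periods correlate at ρ, the SD of the paired difference is s × √(2(1 − ρ)). So s = SD / √(2(1 − ρ)), and equal SDs correspond to ρ = 0.5. Each cell gives power for SD 84.4 / SD 90.4:

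| ρ | s (min) | 12 v 6 | 10 v 5 |
|---|---|---|---|
| 0 | 59.6 / 63.9 | 81% / 75% | 72% / 66% |
| 0.25 | 68.9 / 73.8 | 69% / 63% | 60% / 54% |
| 0.5 | 84.4 / 90.4 | 52% / 47% | 44% / 39% |
| 0.75 | 119.3 / 127.8 | 29% / 26% | 25% / 22% |

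With the stated loss (10 v 5), power is below 80% in every row. Without loss it reaches 80% in one cell only.

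**4. Alternative reading: the 12 as a two-sample total.** Solving for 80% power gives SD 47.3 min (8 v 4), 50.1 min (6 v 6) or, after loss, 44.5 min (5 v 5). The SD that gives 80% power is 60.3 min at 12 v 6 and 54.2 min at 10 v 5. All three implied SDs are smaller, so on this reading the control contrast exceeds 80% and there is no shortfall.

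**5. The 105 min.** 0.22 × 480 = 105.6 min, which reproduces the plan's figure. If the 22% is a relative cut in sitting time:

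| Sitting share of the day | 22% of sitting time (min) |
|---|---|
| 90% | 0.22 × 432 = 95.0 |
| 85% | 0.22 × 408 = 89.8 |
| 80% | 0.22 × 384 = 84.5 |
| 70% | 0.22 × 336 = 73.9 |

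The 90-minute target is below the pilot effect only if the sitting share exceeds 90 / 105.6 = 85.2%. If the 22% means percentage points of the working day, 105 min is correct as it stands.

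**The case against.** The strongest reply is that a power of 40 to 50% is not a figure of this trial. It needs three steps that the document does not state: that 12 is a paired sample size, an SD solved back from it, and the same SD carried into the between-group comparison. Part 3 shows how far the last step matters. If the 80% refers to a difference between two uncorrelated period changes, the ρ = 0 row applies, and 12 v 6 comes to 75 to 81%. If the 12 is a two-sample total, the problem disappears. All of this stands, and a reader who inferred 40 to 50% as a fact would go beyond the documents. Two things remain. The two-sample reading leaves it unexplained why 18 were enrolled when 12 already allowed for loss. On the paired reading, no correlation from 0 to 0.75 restores 80% once the stated loss is applied.

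A reader might also infer that 105 min is an arithmetic slip. The documents do not support that. The pilot report is not shown. The trial's logger measures proportions of time standing and sitting, and the Heartrate variability section assumes 20 to 30% standing, which suits a percentage-point reading. The 80% share is a general remark about office work, not a baseline for this sample. Against this, the pilot result is worded as a reduction of sitting time, which is a relative cut. The wording and the conversion do not agree unless the base is stated.

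Finally, the Discussion concedes that the sample is small and power might be limited, and the general beta sentence may be only a convention. The concession is fair, but it does not say which comparison is weak, and it stands beside a claim that the power analysis is a strength. An SD may also appear in the full protocol, so its absence from an article is not the complaint. The complaint is one 80% figure that reads as covering both contrasts.

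**Conclusion.** The point holds in conditional form. On the natural reading (12 is the experimental arm, tested by a paired t-test), the stated 80% covers only the within-person contrast, with an implied SD of paired differences of 84 to 90 min. The comparison with controls then has 39 to 52% power if the same SD applies. Over correlations from 0.75 to 0 it has 22 to 72% after the stated loss, and 26 to 81% with none. These figures rest on the paired reading, a back-solved SD and normal data with equal variance in the two groups; they do not apply if the 12 is a two-sample total.

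The 90-minute target lies between the stated limits if the 22% is percentage points of the day or if sitting fills more than about 85% of it. On a relative reading at an 80% share, the limits are 77 and 84.5 min, and 90 lies above both.

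This should be corrected because it affects how a null comparison with controls will be read. It does not show that the within-person contrast is underpowered.

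**What to change.** Change the text only; no one need be added.

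- In Sample size, limit the 80% statement to the within-person contrast and give the SD and test actually used.
- State that the comparison with 6 controls is not powered at 80%. Give its power as a range under stated SD and correlation assumptions, recalculated from the real SD; the back-solved figures above should not be published as fact.
- Report that comparison with a 95% CI, so that a non-significant result is not read as no effect. It need not lose its primary status: data collection is over, and demoting it now would be a late change to the outcome.
- In Statistical analysis, keep the two-sided alpha of 0.05 but do not attach a beta risk of 0.2 to all tests.
- State whether the 22% is a share of sitting time or percentage points of the working day. If it is a share of sitting time, correct the 105-minute limit using the pilot's own sitting time, and reword the claim that 90 min lies inside the limits.

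If the 12 was in fact a two-sample total, saying so and giving the SD resolves the power point. The cost is a less favourable power statement.

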### Screening

Study eligibility was determined in private interviews prior to the study. Age, body weight, stature, gender, physical and mental well-being, smoking habits, chronic and acute complaints, pregnancy, medical limitations, medication, working hours per day and week, main occupation and company affiliation were collected via a self-administered questionnaire.

### Intervention for experimental Group

Figure 2 shows the ACTIVE OFFICE two desk sit-to-stand intervention setup. It consists of two equal height-adjustable desks standing next to each other. Precise table arrangements (e.g. 90, 135 and 180°) were self-determined by the participants. To ensure equal conditions, every desk was furnished with the same amount and style of mice, keyboards and screens. Depending on their pre-intervention working conditions, the participants used either one or two screens per desk. The ACTIVE OFFICE was installed 1 day prior to the intervention period at the location of the old desk. Together with the study leader, desk heights were adjusted to the desired sitting and standing heights. Additional software tracking hardware inputs on the standing or sitting desk were installed. The traditional desks were moved to storerooms at the local facility for the duration of the intervention period. During the control phase for the experimental group, both desks were fixed to the sitting height to simulate regular sitting environments. This strategy was used to reduce reconstruction work efforts when the experimental group switched from intervention to control, or vice versa. Reasonable care was been taken to ensure that both desks were equally furnished to avoid preferential effects during both the intervention and control phases (e.g. comparable construction and style of desk, identical equipment and furnishings).

**Fig. 2 Fig2:**
[figure not shown]
ACTIVE OFFICE two desk sit-to-stand intervention setup

### Control group

Control group subjects did not encounter any changes in their regular office environments.

## Outcome measures

Measurements were made both in the field and in a laboratory. Field measurements were made and processed continuously over the 23-week intervention period. Laboratory measurements were made on two different days, 1 day prior to intervention, and 1 day following intervention (due to cross-over design, each subject underwent 4 total days of laboratory measurements). Field measurements were collected automatically at the participants’ workstation in their working office. Laboratory tests were conducted in a controlled, simulated work-space located at the University of Applied Sciences Campus Linz.

### Outcomes

Primary outcomes were changes in sitting time after 23 weeks in the experimental group compared with its own control period and the control group.

Secondary outcomes within the experimental group were changes in: reaction time, working speed, level of attention, workload perception, physical activity and postural changing pattern for the intervention phase as compared to the control phase.

Tertiary outcomes were changes in salivary cortisol level and heartrate variability (HRV) within the experimental group.

### Experimental group: field measurements

Logging-software was installed on each participant’s computer. By recognizing hardware (mouse, keyboard) inputs on either the sitting or standing desk, the software could determine the proportion of time that a subject was standing versus sitting during the 23-week intervention period.

### Experimental group: laboratory measurements

All laboratory measurements were made in a controlled laboratory at the campus site Linz of the University of Applied Sciences Upper Austria. Temperature, air flow, humidity, lighting conditions (artificial light only) and noise level were controlled and set to be consistent with the subjects’ typical working environment.

Participants were asked to refrain from exercise, caffeine and alcohol and undue stress for 24 h prior to laboratory testing. Food intake 90 min prior to the experiment was prohibited. Subjects were instructed to pursue their usual professional activity in the morning, followed by a laboratory visit in the early evening. To avoid daily fluctuations on performance all measurements started between 1:30 and 2:45 pm.

During the laboratory measurements, subjects either stood or sat upright in an ergonomic office chair, according to the study protocol. Subjects were encouraged to work as fast and as accurately as they could. To ensure identical testing conditions between subjects and to not unduly influence physiological parameters such as salivary cortisol level or heart rate variability, subjects were required to minimize excessive movement (e.g. standing up during the sitting periods). During regular breaks subjects were allowed to visit the toilet. Minor body movements, which typically occur under normal working conditions, were allowed.

